### Ethical issues

There are potential but minor risks for providers associated with participating in the study, specifically, feeling coerced into participating, loss of confidentiality, and experiencing discomfort. These risks are addressed in several ways: potential participants are assured that participation is voluntary and will not affect their employment status, all study materials are coded with ID numbers and do not include identifying information, and all data will be maintained in password-protected computer files.

Among caregivers, there is a risk that they may feel uncomfortable with some of the questions in the assessment measures. However, research staff clarify that they do not need to answer any question that makes them feel uncomfortable. The risk to loss of confidentiality is also present for caregivers and is addressed following the same precautions and guidelines used for protecting provider confidentiality. Finally, there is a potential risk that symptoms may worsen as a consequence of the progression of a serious mental health issue or response to a service provided. In the event that this happens, study participation will be halted and appropriate care provided immediately in accordance with clinic procedure.

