### Measures

Data collection will occur at baseline, 8, and 16 weeks from baseline, and at 6-month follow-up. Demographic characteristics about familial factors (e.g., age, race/ethnicity, family income) will be collected via a questionnaire used in prior studies. A separate demographic questionnaire will be administered to providers to gather information including their age, race/ethnicity, education, and credentials.

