*Hypothesis #4*: clinics assigned to MFG + CIT will have more MFGs initiated and completed (with high fidelity and attendance) relative to MFG alone

Overall, the two primary outcomes being tested in this study are changes in child behavior and child functioning. These outcomes are being tested specifically in aims 1 and 2, as measured by the Disruptive Behavior Disorders Rating Scale Oppositional Defiant Subscale [38], Iowa Conners Rating Scale-Oppositional/Defiant Subscale [40] and the Impairment Rating Scale (IRS) [41]. Aims 3 and 4 intend to measure mediators of the primary outcome, by testing clinic readiness and motivation to implement the 4Rs and 2Ss intervention initially and over time, and testing whether fidelity has been adhered to.

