**Fig. 2 Fig2:**
[figure not shown]
Analysis of mechanisms

We will employ mediation analysis with two-level MSEM models as explicated by Preacher, Zhang and Zyphur [57] and extended to three-level models by Preacher [57]. We will use a combination of limited information estimation frameworks (focused on sub-portions of the full model) and full information estimation frameworks (focused on the entire three-level model) to strategically answer questions. At level 1, child outcomes at the immediate post test are modeled as a function of the family predictors (see Fig. 2) using baseline measures of outcomes and family mediators as covariates, taking into account the clustering at the higher levels of the model. The follow-up (6-month) measures of the mediators and the outcomes are included within the model in a classic SEM panel model with autoregressive effects, thereby linking the follow-up data to the immediate post-test data. This is an advantage of using MSEM over traditional multi-level modeling. Different centering strategies (e.g., grand mean versus group mean) can be explored to garner various perspectives on the data. This feature of the model provides perspectives on aim 2 and the relative importance of paths g–l in Fig. 1. To ascertain perspectives of the effects of clinic-level variables on provider variables, random intercept MSEM with the provider-level variables can be estimated as a function of the clinic variables that include dummy coded treatment variables (4Rs and 2Ss MFG + CIT versus 4Rs and 2Ss MFG) impacting the clinic mediators of readiness, leadership support, and climate, which in turn, affect the provider-level intercepts. This modeling, or variants of it, address aims 3 and 4.

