The overall analytic structure requires strategic use of different dummy contrasts and limited information estimation of various MSEM models that map onto the questions dictated by the aims, coupled with judicious use of mediational tests linked to joint significance testing. An alternative analytic structure is to work with all four time periods simultaneously in a classic growth curve model and then to model the linear growth in variables as a function of the provider and clinic variables in strategically defined limited information estimation frameworks dictated by the overall model structure in Fig. 2. We also will explore this approach. Analyses of variable importance (Fig. 1) have been summarized by Tonidandel et al. [58]. Of the two major tools to address the issue (dominance analysis and relative weight analysis), we will use relative weight analysis to gain perspectives because of the less intense computational demands that it makes and its overall flexibility. Missing data will be treated using Full Information Maximum Likelihood (FIML) methods.

A Data Monitoring and Review Board is responsible for reviewing this study’s data to ensure quality and integrity, the safety of participants and study progress, and to make any determinations regarding potential changes to the study. This is comprised of the investigative team with ongoing support from New York University’s Institutional Review Board (IRB). The DMRB meets on a quarterly basis under normal circumstances, or within two business days should an adverse event occur. This process is independent from the sponsors, although they will be notified in the case of a significant change to study protocol or in the case of an adverse event.

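### The rule that halts study participation when symptoms worsen can make loss of the primary outcome depend on the outcome, and FIML as described protects only partly

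*Protocol article*

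**What the plan says.** Ethical issues, in the paragraph on risks to caregivers, allows that "symptoms may worsen as a consequence of the progression of a serious mental health issue or response to a service provided". The consequence follows: "In the event that this happens, study participation will be halted and appropriate care provided immediately in accordance with clinic procedure". No threshold is given, the trigger is not tied to any study scale, and nothing is said about later questionnaires.

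Hypotheses and data analytic strategy states that "the two primary outcomes being tested in this study are changes in child behavior and child functioning", measured by two ODD symptom scales and the Impairment Rating Scale (IRS). The caregiver completes all three. On timing, Measures says: "Data collection will occur at baseline, 8, and 16 weeks from baseline, and at 6-month follow-up".

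Analytic strategy describes a level-1 model in which "child outcomes at the immediate post test are modeled as a function of the family predictors", "using baseline measures of outcomes and family mediators as covariates". The 6-month measures are then linked to the post-test by autoregressive paths. No week-8 outcome appears in that description. An alternative, which the team will also explore, is to "work with all four time periods simultaneously in a classic growth curve model". On missing data there is one sentence: "Missing data will be treated using Full Information Maximum Likelihood (FIML) methods".

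**The concern.** The wording halts participation in the study, not attendance at the groups. Under Description of the conditions, standard-care families receive only what the clinic normally provides, so their study participation consists essentially of the assessments. Halting it can hardly mean anything but ending measurement. Exit is then triggered by symptom worsening in a trial whose primary outcome is symptom change.

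FIML is valid when missingness depends only on observed variables in the fitted model. If worsening is judged clinically between visits and the next score is not taken, missingness depends on a value nobody recorded. The arms may also lose different numbers of dyads for this reason, either because the intervention works or because weekly groups give staff more chances to notice deterioration.

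**Working it through.** **1. Reading the rule.** The article does not say whose symptoms count, but both readings reach the primary outcome. The enrolled unit is the caregiver/child dyad. If the child worsens, loss depends directly on the outcome. If the caregiver worsens, the child's scores are lost with the caregiver's report, and the loss is related to caregiver depression or stress, which the trial also measures.

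**2. What the article gives.** Its only planned size is 2688 dyads, which reproduces: 168 clinics × 0.80 × 20 = 2688, or 3 × 896. It gives no halting rate, threshold, SD, correlation or effect size. Everything below therefore rests on assumptions and shows only how the mechanism behaves.

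**3. Assumptions.** Unit SD at each visit; correlation 0.6 between adjacent visits and 0.5 from baseline to week 16; mean change at week 16 of −0.2 SD in standard care and −0.5 SD in MFG (true contrast −0.30 SD); half of that change by week 8; clustering and family mediators ignored. The estimates come from simulation with 1,000,000 children per arm.

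**4. Worsening not recorded before week 16.** The week-16 score is missing when change from baseline exceeds a threshold *t*. Change has variance 1 + 1 − 2 × 0.5 = 1, so the halted share is 1 − Φ(*t* − μ), where μ is the arm's mean change. For *t* = 1.0 this is 1 − Φ(1.2) = 11.5% in standard care and 1 − Φ(1.5) = 6.7% in MFG.

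With baseline and post-test only, the maximum-likelihood arm mean has a closed form. Put α = *t* − μ, λ = φ(α)/Φ(α), k = αλ + λ² and β = (0.5 + 0.25k)/(1 − 0.25k). The estimated mean is μ − 0.5λ(1 + β). For *t* = 1.0:

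- Standard care: λ = 0.219, k = 0.311, β = 0.627; mean = −0.2 − 0.5 × 0.219 × 1.627 = −0.378.
- MFG: λ = 0.139, k = 0.227, β = 0.590; mean = −0.5 − 0.5 × 0.139 × 1.590 = −0.610.
- Contrast: −0.610 − (−0.378) = −0.232, against −0.30 true.

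The simulation agrees with this. All thresholds, with the dyads implied by 896 per arm:

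| Exit threshold | Halted, standard care | Halted, MFG | Estimate without week 8 | Estimate with week 8 |
|---|---|---|---|---|
| 0.5 SD | 24.2% (217) | 15.9% (142) | 0.19 SD | 0.20 SD |
| 1.0 SD | 11.5% (103) | 6.7% (60) | 0.23 SD | 0.24 SD |
| 1.5 SD | 4.5% (40) | 2.3% (20) | 0.27 SD | 0.27 SD |

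**5. Halting that follows a recorded week-8 score.** With week 8 in the likelihood, the estimate is 0.30 SD at all three thresholds, so FIML recovers the effect. With baseline and post-test only, it is 0.27, 0.28 and 0.29 SD.

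**6. No true effect, worsening unrecorded before week 16, week 8 in the model.** With equal detection the contrast is unbiased (0.00). If worsening is noticed in 80% of cases in MFG and 20% in standard care, a spurious MFG benefit appears: 0.17 SD at the 0.5 SD threshold and 0.09 SD at 1.0 SD. With 90% against 50%, it is 0.14 and 0.07 SD.

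**The case against.** The rule is one safety sentence in a condensed article, and continued follow-up after discontinuation is commonly set out in the full protocol. The sentence sits among caregiver risks, names no study scale and speaks of serious illness, so halts may be few. It is also not stated that assessment stops or that worsening is noticed between visits. All this stands as a limit on how much can be claimed. It does not remove the point, because the sentence is a stated rule, and its plain meaning, above all in standard care, is that measurement ends.

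The calculation in step 4 is also severe. It makes the missing score its own exact trigger, with complete detection in both arms, whereas a clinical judgement would only correlate with that score. The larger thresholds, with fewer halts, are probably closer to a contingency rule, and there the attenuation is about 0.03 SD. That too stands.

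A reader might go further and infer that FIML cannot repair the loss, or that the primary contrast is biased by design whichever way the truth lies. The documents do not support either. Step 5 shows full recovery when halting follows a recorded score that is in the model, and step 6 shows no bias with no effect and equal detection. Nor is it right that the worst outcomes are simply removed: scores taken before a halt stay in the likelihood.

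**Conclusion.** The point holds in conditional form. If a halt ends assessment, loss of the ODD and IRS scores can depend on worsening, and FIML as described protects only so far as that worsening is captured in the fitted model. Leaving week 8 out of the level-1 model weakens that protection.

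The direction cannot be known from the article: toward the null if MFG works and worsening is equally detected, in favour of MFG if worsening is noticed more often in the weekly groups, and none if there is no effect and detection is equal. The size cannot be known either. Under the assumptions in step 3, a true 0.30 SD becomes about 0.20 to 0.27 SD, an attenuation of one third (0.10/0.30) down to one tenth (0.03/0.30). It is small if halting is rare. These figures illustrate the mechanism; they do not forecast this trial. The case for changing the text is that the bias has an unknown sign and is cheap to prevent.

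**What to change.** Leave the care rule as it is and separate it from data collection. State that a halt for worsening does not end outcome assessment: with consent, the caregiver questionnaires at 8 weeks, 16 weeks and the 6-month follow-up continue, and the dyad is analysed in its allocated arm. Say whether the child's or the caregiver's worsening is meant, and record the date and reason of each halt by arm, so that unequal detection can be seen.

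Keep week 8 in the primary likelihood, and not only in the growth-curve alternative. For scores still missing after a halt, add a missing-not-at-random sensitivity analysis, for example delta-adjusted, with the shift allowed to differ between arms.

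The cost is protocol and consent wording, a few more questionnaires from families already enrolled, and one extra analysis. Continued collection removes this source of loss only so far as halted families agree to answer, which is why the sensitivity analysis is still needed.

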## Discussion

This study represents an innovative approach to examine the uptake and sustainment of a National Registry of Evidence-based Programs and Practices (NREPP)-approved, evidence-based treatment for child DBDs, and the organizational factors that impede or facilitate adoption of EBPs in public mental health settings. This study will also examine a novel approach to adapt an EBP in a structured way, in order to enhance its fit with the needs of the populations being served and the organizational context. One of the strengths of this study is that it will test uptake across the entire child-serving, public mental health service system in the five boroughs of NYC.

The study aims to generate knowledge needed to address seemingly intractable urban service delivery challenges, including lack of engagement of low-income youth with serious DBDs and their families, too few clinics offering family based, evidence-informed services; lack of scalable, empirically supported interventions designed for resource-strapped child settings; and few empirically supported options for public policy-makers to support the uptake and integration of service innovations within behavioral health care.

### Trial status

Clinic recruitment for standard care has been completed. Data collection has been initiated, and one third (*n* = 792) of the sample of providers and caregivers have been enrolled. Clinic recruitment for MFG and MFG + CIT have been initiated, and some clinics have already completed training and have participated in adaptation meetings. Recruitment of clinics for the experimental arms will be ongoing until enrollment targets are met. Groups for both MFG and MFG + CIT are expected to begin in the first trimester of 2017. A populated Standard Protocol Items: Recommendations for Interventional Trials (SPIRIT) Checklist (see Additional file 1) and Figure ( see Fig. 3) for all study protocols are included as an additional file (see Additional file 1 and Fig. 3). A composition of the data monitoring commitee has also been included (see Additional file 2).

**Fig. 3 Fig3:**
[figure not shown]
SPIRIT Checklist

## Abbreviations

APQ-9: Alabama Parenting Questionnaire nine-item short form
CESD: Center for Epidemiologic Studies Depression Scale
CIT: Clinic Implementation Team
DBD: Disruptive behavior disorder
EBP: Evidence-based practice
FAD: McMaster Family Assessment Device
IOWA CRS: Iowa Conners Rating Scale
IRS: Impairment Rating Scale
KBT: Kazdin Barriers to Treatment
MFG: Multiple Family Group
MSEM: Multi-level Structural Equation Modeling
MSPSS: Multidimensional Scale of Perceived Social Support
NREPP: National Registry of Evidence-based Programs and Practices
NYC: New York City
NYSOMH: New York State Office of Mental Health
OD: Oppositional defiant
ODD: Oppositional defiant disorder
PSI: Parenting Stress Index
SAMHSA: Substance Abuse and Mental Health Services Administration
SEM: Structural Equation Modeling
TCU ORC: Texas Christian University Organizational Readiness for Change
